### Composition of sample

The required sample size was determined for the primary outcome variable, that is, overall score of the Fibromyalgia Impact Questionnaire (FIQ). According to Bennett *et al*. [20], a clinically relevant change is a 15 to 20% reduction in the total FIQ score (which is equal to an approximate 10 to 15 points reduction). Assuming a unilateral alternative (that is, the intervention reduces the impact of fibromyalgia), we can detect differences of at least 15% with a power of 95% and α of 0.05 with two groups (intervention and usual control group) of 45 participants, with a mean in the FIQ of approximately 70 and a standard deviation of approximately 20 points. Assuming a maximum loss of follow-up of 30%, we will recruit a total of 60 women with fibromyalgia for each group. We will recruit a total of 120 women with fibromyalgia (that is, one LLLT intervention group and control group of 60 persons each).

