#### Pressure algometry of pain threshold

A pressure algometer (digital algometer, model DDK 20, manufactured by Kratos Ltd., Cotia, Sao Paulo, Brazil) is a device that assesses the pain threshold. This device consists of a round rubber disk (1 cm^2^) attached to a pressure (force) gauge. The gauge displays values in kilograms. Because the surface of the rubber tip is 1 cm^2^, the readings are expressed in kilogram per square centimeter (kg/cm^2^). The range of the algometer is 0 to 10 kg and records in 0.1 kg divisions. At one end of the device, perpendicular pressure is applied to the surface of the skin and recorded using a manometer. The algometry of the pain threshold on the tender points will be performed based on the fibromyalgia classification criteria of the ACR, following the procedures described below:

•The patient will be asked to sit in a chair with feet supported on the ground and hands supported on the lap;

•The tender points will be marked with a skin marking pen and evaluated bilaterally in the following order: occipital, anterior lower cervical, trapezius, supraspinatus, second costochondral joint, lateral epicondyle and medial edge of the knee;

•The patient will be instructed to remain in an orthostatic position and the tender points of the gluteus and greater trochanter will be marked with the pen, bilaterally;

•During the assessment of the pain threshold on the tender points, perpendicular pressure will be applied to the surface of the skin and increased gradually in increments of 0.1 kg until the patient reports feeling pain;

•Positive results will be those below 2.6 kg/cm^2^, which is equivalent to the 4.0 kg/cm^2^ described in studies by Wolfe *et al*. [21].

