#### McGill Pain Questionnaire

The McGill Pain Questionnaire (MPQ) adapted to the Portuguese language will be used [23]. The questionnaire consists of a list of 78 pain descriptors organized into 4 major categories (sensory, affective, evaluative, and miscellaneous) and 20 subcategories, each made up of at least 2 and up to 6 words, to which intensity values are assigned. To calculate Pain Rating Index (PRI) the descriptors of the third category, which characterizes pain, will be used. Present Pain Intensity (PPI) will be evaluated using a verbal scale of pain (0 - no pain, 10 - very strong pain).

As some patients may have difficulty reading and understanding the instructions of the questionnaires (McGill Pain Questionnaire, SF-36 and FIQ), the reading will be performed together with the researchers.

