### Evaluation of results

The intention-to-treat analysis will be followed. The patients will be evaluated with regard to the primary outcome (pain) using the visual analog scale for pain, the McGill Pain Questionnaire and pressure algometry. The secondary outcome (quality of life) will be assessed using the SF-36 and FIQ. The use of medication will be controlled throughout the study. The data on the use of analgesics and daily dosage of adjuvant therapy, such as antidepressants and muscle relaxers, will be recorded and tabulated.

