### Statistical analysis

ANOVA test with repeated measurements for the time factor will be performed to test between-groups differences (followed by the Tukey-Kramer post hoc test), and a paired *t* test will be performed to test within-group differences. The level of significance for the statistical analysis will be set at 5% (*P* ≤0.05).

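### Three pain instruments (at least four scores) are jointly primary with no lead score, success rule or error control across them, and the sample size section names the FIQ as primary instead

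*Protocol article*

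**What the plan says.** **Primary outcome.** Evaluation of results assesses the "primary outcome (pain) using the visual analog scale for pain, the McGill Pain Questionnaire and pressure algometry". The Abstract names the same three instruments. Neither ranks them.

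**Scores within the instruments.** The McGill section takes two scores: "To calculate Pain Rating Index (PRI) the descriptors of the third category, which characterizes pain, will be used", and "Present Pain Intensity (PPI) will be evaluated using a verbal scale of pain". For algometry, "The algometry of the pain threshold on the tender points will be performed based on the fibromyalgia classification criteria of the ACR". Nine sites are measured on both sides, which makes 18 readings per patient. A cut-off for a positive reading is given (2.6 kg/cm²), but no single value per patient is named for analysis.

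**Testing.** Under Statistical analysis, "ANOVA test with repeated measurements for the time factor will be performed to test between-groups differences (followed by the Tukey-Kramer post hoc test"), with paired *t* tests within groups. Then: "The level of significance for the statistical analysis will be set at 5"%. The Abstract gives the same analysis and level.

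**A second primary outcome.** Under Composition of sample: "The required sample size was determined for the primary outcome variable, that is, overall score of the Fibromyalgia Impact Questionnaire (FIQ"). Evaluation of results and the Abstract both place the FIQ among the secondary measures.

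**The concern.** A 5% level describes the error rate of a conclusion only if the plan says which result, or which combination of results, supports that conclusion. Here several scores share the primary role, and the article does not say what counts as a positive trial. The Tukey-Kramer step handles pairwise comparisons within one ANOVA. It does not act across VAS, McGill and algometry.

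At stake is whether a claim of analgesia carries the stated 5%. A report that relied on whichever pain score reached significance would carry more than that, and nothing in the text rules such a report out. The FIQ statement adds to the problem, because which claim the 5% protects is itself unsettled. The only sample size calculation in the article is for the FIQ, so none of the pain scores has a stated power basis.

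**Working it through.** **Inputs from the protocol article**
- Primary instruments: 3 (Evaluation of results; Abstract).
- Scores: VAS, McGill Pain Rating Index (PRI), McGill Present Pain Intensity (PPI) and at least one algometry value, so at least 4.
- Level: 5% (Statistical analysis).

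**Assumptions, not in the article**
- Two-sided tests.
- A common correlation *r* between the test statistics. No correlation is given, so a range is shown.
- Success means at least one significant score. This is one of two possible rules, and the article states neither.

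**Step 1: the plan's own figure.** One score at 5% gives 1 − 0.95 = 5%. The stated level is right for a single named primary.

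**Step 2: any one of *k* independent scores suffices.** The rate is 1 − 0.95^*k*.
- *k* = 3: 1 − 0.8574 = 14.3%
- *k* = 4: 1 − 0.8145 = 18.5%

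**Step 3: the same rule with equal correlation.** With *c* = 1.960, Φ the standard normal distribution function and φ its density,

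rate = 1 − ∫ [Φ((*c* − √*r*·*u*)/√(1 − *r*)) − Φ((−*c* − √*r*·*u*)/√(1 − *r*))]^*k* φ(*u*) d*u*

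| *r* | 3 scores | 4 scores |
|---|---|---|
| 0 | 14.3% | 18.5% |
| 0.2 | 14.0% | 18.0% |
| 0.5 | 12.5% | 15.6% |
| 0.7 | 10.9% | 13.0% |
| 0.8 | 9.8% | 11.4% |
| 0.9 | 8.4% | 9.4% |

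The sample size section uses a one-sided alternative. One-sided 5% tests on four scores give 17.2% at *r* = 0.2 and 10.6% at *r* = 0.8, so sidedness changes little.

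**Step 4: all scores must succeed.** If at least one score has no true effect, the chance that all are significant cannot exceed the chance that this one is. The rate is therefore at most 5%.

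**Step 5: restoring 5%.** Bonferroni on three scores uses 0.05/3 = 0.0167 each, and 1 − (1 − 0.0167)³ = 4.9% under independence. Holm starts at the same 0.0167, then uses 0.05/2 = 0.025, then 0.05.

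**Step 6: the power basis.** The only calculation is for the FIQ: mean 70, SD 20, one-sided 5%, power 95%, 45 per group. With *n* = 2(1.645 + 1.645)² × 20²/δ²:
- δ = 15% of 70 = 10.5 points: *n* = 79 per group; 45 per group gives 80% power.
- δ = 20% of 70 = 14 points: *n* = 45 per group.

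The stated 45 matches a 20% difference, not the 15% in the text. This matters here only because the calculation would need checking if the FIQ were kept as primary.

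**The case against.** The strongest reply is that no inflated error rate follows from the text. The article never says that one significant score is enough. Its Discussion lists the expected results together (lower VAS pain, higher pressure threshold, better quality of life and sleep), which fits an all-required reading at least as well. Under that reading the rate is at most 5%. This stands: a reader might infer that the trial's false-positive rate simply is 11–18%, and the documents do not support that as a plain fact.

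The correlations are also assumed, and some are probably high. VAS asks about pain at the moment of marking and PPI rates present pain, so those two measure nearly the same thing. This also stands, and it argues against the top of the range. Even at *r* = 0.9, however, four scores give 9.4% under the any-one rule.

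Third, a condensed article may leave adjustment across endpoints and the algometry summary to an analysis plan that is not shown. This stands in part. A reader might infer that each score, or each of the 18 sites, will be tested separately without adjustment, but the article does not say so. The choice of primary outcome is different: this article makes it. It names three instruments twice and a fourth, different measure for the sample size. That is a choice fixed badly, not a missing detail.

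The Discussion is an expectation, not a decision rule, and it does not mention the McGill. An all-required rule is therefore not evident either.

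**Conclusion.** The point holds in conditional form. The article makes at least four pain scores jointly primary, gives neither a lead score nor a success rule, states one 5% level with no control across instruments, and elsewhere names the FIQ total as the primary outcome variable.

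How far the error rate departs from 5% depends on the missing rule. If any one of four scores suffices, it is about 11–18% for correlations of 0.8 to 0.2, with 18.5% under independence. Three scores give about 10–14% for correlations of 0.8 to 0. If all must succeed, it is at most 5%. The any-one rule and the correlations are assumptions, and the range is not a bound. What the text does establish is that it does not determine which of these rates applies, or whether the primary claim concerns pain or the FIQ.

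**What to change.** Before unblinding:
1. Name one primary score at the end of the program, tested at 5% with the sidedness stated. VAS is an example; nothing in the article ranks the instruments.
2. Test the others in a fixed sequence at 5%, for example mean pressure threshold over the 18 sites as one value per patient, then McGill PRI. Confirmatory claims stop at the first non-significant result. If the instruments are meant to be co-equal, use Holm across three prespecified scores instead.
3. Report PPI and single sites descriptively.
4. Reconcile Composition of sample in one of two ways. Either make the FIQ total the single primary, with the pain scores as ordered secondaries, and check its calculation (Step 6). Or make the pain score primary and restate the power basis for that score at the planned 60 per group.

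The edits fall in the Abstract, Evaluation of results, Statistical analysis and Composition of sample. Changing only the outcome and analysis sections would leave two competing primaries, and a pain primary with no stated power. No extra data are needed. Patients were being recruited at submission, but the active and placebo probes are identified only after data acquisition, so the choice can still be made blind.

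The cost is that later scores can be claimed only if earlier ones succeed or, under Holm, that the first test must pass 0.0167 and the second 0.025.

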### Statistical analysis

ANOVA test with repeated measurements for the time factor will be performed to test between-groups differences (followed by the Tukey-Kramer post hoc test), and a paired *t* test will be performed to test within-group differences. The level of significance for the statistical analysis will be set at 5% (*P* ≤0.05).

## Discussion

According to data obtained from World Health Organization, a large number of people around the world suffer with chronic pain and it reflects in physical incapacity related to work activities. Furthermore, chronic pain represents a limiting factor in quality of life in modern society. Recent studies have shown that 10% of world population suffers with diffuse chronic pain, and 2 to 5% of these cases are related to fibromyalgia [26-28].

Billions of American dollars are expended around the world every year in diagnostics, treatment, lost workdays and judicial process due chronic pain. In some cases, the cause of pain can be due fibromyalgia. Therefore, the development of efficient therapies can also represent an important decrease in financial costs in relation to chronic pain related to musculoskeletal disorders [29-31].

LLLT has been widely used in treatment of skeletal muscle disorders with positive results [32-35]. The light-tissue interaction (photobiostimulation) leads to analgesic and anti-inflammatory effects [36], and also improves tissue healing [37]. With this perspective in mind, we can expect that LLLT in addition to exercise will significantly decrease pain and improve quality of life in these patients.

Finally, with the development of the protocol of this study, it is expected that the group treated with LLLT will present with significant reduction of pain intensity on the visual analog scale, increase in the pressure pain threshold, and improvement in the overall quality of life and quality of sleep.

## Trial status

At the time of manuscript submission the patients are being recruited to trial.
